## 8.9.1 Adverse Events

All AEs will be classified by Primary SOC and PT according to MedDRA Version 25.0 or higher and will be graded according to the National Cancer Institute Common Terminology Criteria for Adverse Events (NCI CTCAE) version 5.0.

AEs will be summarized by SOC and PT using counts and percentage (i.e., number and percentage of participants with an AE). AEs will be sorted by decreasing frequency within each SOC and PT as per the overall column.

Where a participant has the same AE, based on PT reported multiple times, the participant will only be counted once at that PT level. Where a participant has multiple AEs within the same SOC, the participant will only be counted once at that SOC level.

If a participant experiences the same AE more than once with different severity grades, then the event with the highest severity will be tabulated by maximum severity. In addition, AEs with a missing severity will be presented in the summary table under the category of ‘Missing’ and will not be imputed.

TEAEs are defined as any AE occurring or worsening on or after the first dose of study treatment.

TEAEs will be assigned to Part A, Part B and Part A+B using the event start date and time and will be defined as:

- Part A: events started on or after the first dose of study medication for Part A but not after Part B or events present prior to the first dose of study medication for Part A but increased in severity on or after dosing on Part A but not after Part B
- Part B: events started on or after the first dose of study medication for Part B or events present prior to the first dose of study medication for Part B but increased in severity on or after dosing on Part B

For Part A+B treatment emergent AEs relating to the Part when the subject was on the corresponding treatment are considered as TEAE.

Adverse events with an onset on Day 1 which are based upon pre-dose lab tests will be considered as not treatment emergent. These are defined as:

- Adverse events which begin on study day 1 with SOC = “Investigations” or PT in (“Hypercholesterolaemia” “Hyperlipidaemia” “Dyslipidaemia”, “Type V hyperlipidaemia”).
- The latest lab test taken on Day 1 has a time which is before the treatment start time.

Treatment-related AEs are those events with relationship to study drug ‘Related’ as recorded on the CRF. If the relationship to study drug is missing, the AE will be considered as treatment related.

Details for imputing missing or partial start dates of AEs are described in [Section 8.3.2](#).

Separate summary tables by treatment will be presented with the total number of events and number and percentage of participants with:

- All TEAEs
- Grade 3/4/5 TEAEs
- TEAEs by maximum intensity
- Related TEAEs
- TEAE leading to treatment discontinuation

- TEAE leading to study discontinuation
- Serious adverse events (SAEs)
- Related SAEs
- Fatal AEs
- AESI.

AEs by DSUR safety topics (Hypersensitivity reactions SMQ; Opportunistic Infections SMQ; Gastrointestinal nonspecific inflammation and dysfunctional conditions SMQ). Where a participant has the same AE, based on PT reported multiple times, the participant will only be counted once at that PT level. Where a participant has multiple AEs within the same SMQ, the participant will only be counted once at that SMQ level. AEs by DSUR safety topics will only be presented for DSUR analysis.

An overall summary presenting the categories above will also be prepared by treatment group for Part A, Part B, and Part A+B. In addition, the total number of participant treatment years and exposure adjusted incidence rates [EAIR] will be provided as described in [Appendix J](#).

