#### **12.3.4.1 Adverse Events**

A summary table will be presented with total number and number of participants with the following:

- TEAEs;
- SAEs;
- Related TEAEs;
- Related SAEs;
- TEAEs leading to discontinuation;

- AESI;
- Fatal AEs.

TEAEs will be described using descriptive statistics and coded according to the Medical Dictionary for Regulatory Activities (MedDRA) system organ class (SOC) and MedDRA preferred term (PT), by treatment arms. Drug-related TEAEs and SAEs will also be summarized by treatment arms. Incidence rates of TEAEs during Part B and for the combined Part A + Part B analysis will be adjusted for exposure duration to study treatment (i.e., exposure adjusted incidence rates [EAIR]).

AEs will also be tabulated by intensity and relationship to treatment (“not related/related”).

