- Sonelokimab 120 mg Q2W→sonelokimab 120 mg Q4W;
- Sonelokimab 120 mg Q2W→adalimumab 40 mg Q2W;
- Sonelokimab 60 mg Q2W→sonelokimab 60 mg Q4W;
- Sonelokimab 60 mg Q2W→sonelokimab 120 mg Q4W;
- Sonelokimab 60 mg Q4W→sonelokimab 60 mg Q4W;
- Sonelokimab 60 mg Q4W→sonelokimab 120 mg Q4W;
- Placebo→sonelokimab 120 mg Q4W;
- Adalimumab 40 mg Q2W→adalimumab 40 mg Q2W;
- Adalimumab 40 mg Q2W→sonelokimab 120 mg Q2W.
- Total sonelokimab (safety tables only)

**Part A+B:** For Part A+B no statistical testing will be performed. Summary statistics will be based on the data collected from the visit Week 0 to Week 24. Part A+B tables will only be presented for adverse events.

Unless otherwise stated, the summary statistics will be presented for the following treatment groups:

- Placebo (Part A only)
- Total Sonelokimab 120mg
- Total Sonelokimab 60mg
- Total Adalimumab 40mg Q2W
- Total Sonelokimab

For the total groups they will have different subjects potentially for Part A and Part B and subjects will only have results shown for the Part when they took the relevant treatment.

All participant data, including those derived, will be presented in individual participant data listings. Unless otherwise stated, unscheduled visit results will be included in date/time chronological order, within participant listings only. All listings will be sorted by treatment group, investigational site, participant number, date/time, and visit. The treatment group as well as participant's sex, age and race will be stated on each listing. Unless otherwise stated, safety data listings will be based on SAF and efficacy data listings will be based on FAS.

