## 8.9 Safety Analyses

For all the safety endpoints, no formal statistical testing will be performed. Safety summaries will be presented by treatment group separately for the Part A (SAF), Part B (SAF-Part B), and Part A+B (SAF).

For Part A, 6 groups will be considered:

- Sonelokimab 120 mg (Q2W),
- Sonelokimab 60 mg (Q2W),
- Sonelokimab 60 mg (Q4W),
- Placebo,
- Adalimumab 40 mg (Q2W),
- Total sonelokimab.

For Part B and follow-up period, 10 groups will be considered:

- Sonelokimab 120 mg Q2W→sonelokimab 120 mg Q4W;
- Sonelokimab 120 mg Q2W→adalimumab 40 mg Q2W;
- Sonelokimab 60 mg Q2W→sonelokimab 60 mg Q4W;
- Sonelokimab 60 mg Q2W→sonelokimab 120 mg Q4W;
- Sonelokimab 60 mg Q4W→sonelokimab 60 mg Q4W;
- Sonelokimab 60 mg Q4W→sonelokimab 120 mg Q4W;
- Placebo→sonelokimab 120 mg Q4W;

- Adalimumab 40 mg Q2W→adalimumab 40 mg Q2W;
- Adalimumab 40 mg Q2W→sonelokimab 120 mg Q2W.
- Total sonelokimab

For Part A+B, 5 groups will be considered:

- Placebo (Part A only)
- Total Sonelokimab 120mg
- Total Sonelokimab 60mg
- Total Sonelokimab
- Total Adalimumab 40mg Q2W

The placebo group will include all subjects who were randomized to placebo in Part A and will only include Part A summary visits.

The total Sonelokimab 120mg group will include all subjects who were randomized to Sonelokimab 120mg Q2W in Part A and subjects who had Sonelokimab 120mg Q2W or Q4W in Part B. Subjects will only be included for summary visits during the Part they were assigned 120mg Q2W.

The total Sonelokimab 60mg group will include all subjects who were randomized to Sonelokimab 60mg Q2W or Q4W in Part A and subjects who had Sonelokimab 60mg during part B (Sonelokimab 60mg Q2W responders and Sonelokimab 60mg Q4W responders). Subjects will only be included for summary visits during the Part they were assigned Sonelokimab 60mg.

The total Adalimumab 40mg Q2W group will include all subjects who were randomized to Adalimumab 40mg Q2W during Part A and subjects who had Adalimumab 40mg Q2W during part B (Adalimumab 40mg Q2W responders and Sonelokimab 120mg Q2W non-responders).

The total Sonelokimab arm will include subjects who received sonelokimab at any time in the study. Subjects will only be included for summary visits during the Part they were assigned Sonelokimab.

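### The Part A+B adverse-event tables set 12 weeks of placebo beside up to 24 weeks of pooled sonelokimab as crude percentages, and the exposure adjustment is not clearly carried to term level

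*Combined protocol and SAP*

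**What the plan says.** SAP 8.1 restricts the combined set to safety events: "Part A+B tables will only be presented for adverse events". It gives the time span as "Summary statistics will be based on the data collected from the visit Week 0 to Week 24".

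SAP 8.9 lists five columns: placebo (Part A only), Total Sonelokimab 120 mg, Total Sonelokimab 60 mg, Total Sonelokimab and Total Adalimumab. On placebo it says "The placebo group will include all subjects who were randomized to placebo in Part A and will only include Part A summary visits". On the main pooled column it says "The total Sonelokimab arm will include subjects who received sonelokimab at any time in the study", with each participant contributing only the Part or Parts in which sonelokimab was assigned.

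SAP 8.9.1 specifies the SOC/PT tables as "AEs will be summarized by SOC and PT using counts and percentage (i.e., number and percentage of participants with an AE". It also asks for the number and percentage of participants for Grade 3–5, related, discontinuation, serious, fatal and special-interest events. Exposure-adjusted incidence rates (EAIR) appear once, directly after this sentence: "An overall summary presenting the categories above will also be prepared by treatment group for Part A, Part B, and Part A+B".

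Protocol 12.3.4.1 is broader: "Incidence rates of TEAEs during Part B and for the combined Part A + Part B analysis will be adjusted for exposure duration to study treatment". SAP Section 9 lists changes from the protocol and mentions none on this point.

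**The concern.** A crude percentage depends on how long each participant is watched. If one column is watched for 12 weeks and the next for up to 24, the longer one shows more participants with an event even when the drug does nothing. The safety objective is sonelokimab compared with placebo, and these tables put the two side by side by preferred term and event category. The error runs against sonelokimab: it can suggest a signal that is only extra observation time. Pooled columns are also a natural place to look for uncommon events, where the ratio is largest.

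**Working it through.** **The plan's own time figures.** SAP 3.3 gives planned durations of 34 weeks (non-US) and 22 weeks (US). Screening + week of last dose + follow-up gives 4 + 22 + 8 = 34 and 4 + 10 + 8 = 22, so both reproduce. The plan states no pooled exposure and no expected event ratio.

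**Inputs.** There are 40 participants per arm (sample-size section). Part B allocation follows SAP Table 1:
- Arms 2 and 3 stay on sonelokimab.
- Arm 1 responders stay; Arm 1 non-responders move to adalimumab.
- Placebo participants and Arm 5 non-responders start sonelokimab at Week 12.
- US participants stop after Part A (SAP 3.1).

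Assumed, because the documents do not give them: Week 12 joint-count response of 50–80%, US share of 0–40%, constant and equal hazards, and no dropout.

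**Formula to Week 24.** Let p be the 12-week risk. A participant counted for 12 weeks has risk p. One counted for 24 weeks has risk 1 − (1 − p)² = p(2 − p). If a fraction f of a pooled column is counted for 24 weeks and the rest for 12, the crude ratio to 12-week placebo is (1 − f) + f(2 − p) = 1 + f(1 − p).

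**Total Sonelokimab, no US participants, 50% responders.** Counted for 24 weeks: 20 (Arm 1) + 80 (Arms 2 and 3) = 100. Counted for 12 weeks: 20 (Arm 1) + 40 (Arm 4) + 20 (Arm 5) = 80. Mean time = (100 × 24 + 80 × 12)/180 = 18.7 weeks, and f = 100/180 = 0.556. For p = 5% the column shows (100 × 0.0975 + 80 × 0.05)/180 = 7.6% against 5.0% on placebo.

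The same steps for the corners of the assumed range:

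| US share | Responders | n at 24 wk | n at 12 wk | Mean wk | f | Ratio, p = 1% | p = 5% | p = 10% | p = 30% |
|---|---|---|---|---|---|---|---|---|---|
| 0 | 50% | 100 | 80 | 18.7 | 0.556 | 1.55 | 1.53 | 1.50 | 1.39 |
| 0 | 80% | 112 | 56 | 20.0 | 0.667 | 1.66 | 1.63 | 1.60 | 1.47 |
| 40% | 50% | 60 | 96 | 16.6 | 0.385 | 1.38 | 1.37 | 1.35 | 1.27 |
| 40% | 80% | 67.2 | 81.6 | 17.4 | 0.452 | 1.45 | 1.43 | 1.41 | 1.32 |

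**Dose pools to Week 24** (the same 50–80% also assumed in Arms 2 and 3). In the 120 mg pool most participants contribute one Part only. f runs from 12/100 (40% US, 50% responders) to 32/104 (no US, 80%), so for p of 1–10% the ratio is 1.11–1.30. In the 60 mg pool f runs from 24/80 to 64/80, giving 1.27–1.79.

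**If follow-up counts.** The Part B rule in SAP 8.9.1, "events started on or after the first dose of study medication for Part B or events present prior", has no end date. On that reading, non-US participants on sonelokimab in Part B gain 6 weeks (Week 24 to Week 30). US participants, including US placebo, are counted to Week 18. With no US participants and 50% responders, mean time is (100 × 30 + 60 × 18 + 20 × 12)/180 = 24.0 weeks. For p = 5% the column shows (100 × 0.1203 + 60 × 0.0741 + 20 × 0.05)/180 = 9.7%, a ratio of 1.94. Across the same assumptions and p of 1–10%, the ratio is 1.48–2.13. At 40% US, mean placebo time is itself 0.6 × 12 + 0.4 × 18 = 14.4 weeks.

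**Check of the remedy.** With rates taken as participants with an event over time to first event or end of observation, p = 5% gives 22.3 per 100 participant-years in both columns. Limiting both columns to Part A also returns a ratio of 1.00.

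**The case against.** The plan already deals with unequal time in two places. Separate Part A safety tables show placebo and Total Sonelokimab over the same randomised 12 weeks, and the Part A+B placebo column carries its limit in its label. EAIR is planned too. The SAP sentence on it opens afresh, and Appendix K defines the rate for any event, so it could be meant for every table. The table shells are in a separate document that is not available here. Safety is descriptive, with no testing.

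Much of this stands. A reader might infer that the SAP has dropped the protocol's exposure adjustment without declaring it. The documents do not establish that: the scope of the EAIR sentence is unclear, and confining it to the overall summary is an inference from where it sits. Nor does the protocol require confidence intervals or a rate in every table; it speaks only of TEAE incidence rates.

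A reader might also infer a general 1.5- to 2-fold excess, or that every row will look worse on sonelokimab. Neither follows. The ratio falls with event frequency, US share and choice of pool, and a value near 2 needs a follow-up reading that conflicts with the Week 0 to Week 24 span in SAP 8.1. With 40 placebo participants, a 1% event has 0.4 expected cases, so chance decides many single rows.

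What remains is that the term-level and category tables, as written, show crude percentages beside a shorter placebo window. The cross-reference that should lead to the remedy points to Appendix J, which lists laboratory tests; the rate is defined in Appendix K.

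**Conclusion.** The point holds in limited form. Followed as written, the Part A+B term-level and category tables give a time-biased comparison with placebo. Under the stated assumptions the expected excess with no drug effect is about 1.35–1.7 for events with a 12-week risk of 10% or less in Total Sonelokimab to Week 24. It is about 1.1–1.3 in the 120 mg pool. For a 30% event in Total Sonelokimab it is about 1.27–1.47. About 1.5–2.1 applies only if follow-up events count, and SAP 8.1 and 8.9.1 disagree on that. The Part A comparison is unaffected. The sizes rest on assumed response rates and US share; the direction rests only on the longer sonelokimab window.

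**What to change.** In SAP 8.9.1, choose one of two options for each Part A+B adverse-event table with a placebo column (SOC/PT, serious, special-interest, related, Grade 3–5, discontinuation):
- report EAIR beside the number of participants, counting only events with onset inside the person-time in the denominator; or
- drop the placebo column from the crude-percentage version.

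The onset condition matters because Appendix K runs observation to the last Part B visit for everyone randomised to sonelokimab. That includes Arm 1 non-responders who are on adalimumab in Part B, whereas SAP 8.9.1 attributes events by the treatment of each Part.

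Also state that the 12-week Part A tables are the sonelokimab-versus-placebo safety comparison, reconcile SAP 8.1 with 8.9.1 on whether follow-up events count in Part A+B, and correct the appendix reference. Confidence intervals for the rates are optional.

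The cost is SAP and shell wording, a little programming, and wider tables or one lost column. No new data are needed.

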### **8.3.3 Week 12 Visit**

Assessments at Week 12 are both the final assessments for Part A and the first assessments for Part B. The dose administered at Week 12 is the first dose for Part B. The last dose administration is scheduled for Week 22.

At Week 12 (at the beginning of Part B) TJC68 and SJC66 response will be assessed in all participants. A responder is defined as a participant who achieves at least a 20% reduction in each of TJC68 and SJC66 assessments at Week 12 compared with baseline. A non-responder is defined as a participant who does not achieve at least a 20% reduction in each of TJC68 and SJC66 assessments at Week 12 compared with baseline.

Treatment assignments in Part B will be allocated based upon response at Week 12 via the IRT as indicated in [Figure 1](#) and described in Section [10.1](#).

In the event a participant does not attend Week 12, please refer to Rescheduling Visits in Section [8.6](#).

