#### **12.3.4 Safety Analyses**

For any of the safety endpoints, listed in Section 7.2.6, no formal statistical testing will be performed.

Safety analyses will be done separately for Part A and Part B. AEs will be assigned to either Part A or Part B using the event start date and time. AEs that start after first treatment of Part B will be used within the Part B analysis. For Part A, 5 arms will be considered:

- Arm 1: sonelokimab 120 mg Q2W;
- Arm 2: sonelokimab 60 mg Q2W;
- Arm 3: sonelokimab 60 mg Q4W;
- Arm 4: placebo;
- Arm 5: adalimumab 40 mg Q2W.

For Part B or for the whole treatment period, 9 arms will be considered:

- Sonelokimab 120 mg Q2W→sonelokimab 120 mg Q4W;
- Sonelokimab 120 mg Q2W→adalimumab 40 mg Q2W;
- Sonelokimab 60 mg Q2W→sonelokimab 60 mg Q4W;
- Sonelokimab 60 mg Q2W→sonelokimab 120 mg Q4W;
- Sonelokimab 60 mg Q4W→sonelokimab 60 mg Q4W;
- Sonelokimab 60 mg Q4W→sonelokimab 120 mg Q4W;
- Placebo→sonelokimab 120 mg Q4W;
- Adalimumab 40 mg Q2W→adalimumab 40 mg Q2W;
- Adalimumab 40 mg Q2W→sonelokimab 120 mg Q2W.

Participants will be followed for safety until the end of the Safety Follow-up Visit (or until withdrawal from the study, whichever is later).

The SAF will be used for all safety analyses.

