**If only Day of AE start date is missing:**

If the AE start year and month are the same as that for the first dose date, then:

- If the full (or partial) AE end date is NOT before the first dose date or AE end date is missing, then impute the AE start day as the day of first dose date; otherwise, impute the AE start day as 1.

If the AE start year and month are not same as that for the first dose date, then, impute the AE start day as 1.

Compare the imputed AE start date with treatment-emergent (TE) period to determine whether the AE is pre-treatment AE, treatment-emergent adverse event (TEAE) or post-treatment AE.

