## 8 STATISTICAL METHODS

### 8.1 General Statistical Conventions

All statistical procedures will be completed using SAS version 9.4® or higher.

For continuous variables, descriptive statistics (number of observations, mean, standard deviation (SD), minimum (min), first quartile, median, third quartile and maximum (max) and 95% confidence intervals (CIs) as appropriate) will be presented. Summaries of hs-CRP and PK concentration will include the geometric mean (GM) and coefficient of variation (CV). The count of missing observations will be provided in all descriptive tables.

Categorical variables will be presented as counts and percentages with non-missing values in each category. The number of missing values will be presented as a separate category, if there is at least one missing value. Unless otherwise stated, all statistical testing will be two-sided and will be performed using a significance (alpha) level of 0.05. For all statistical analyses, p-values and 95% CIs will be provided. All sensitivity analyses will be regarded as exploratory and as such no formal adjustment for multiplicity will be made.

Number of decimal places will be presented as follow:

- continuous variables: for min and max, the decimals will be used as captured in the database; arithmetic mean, median and quartiles will be depicted with one more decimal than captured in the database; and SD will be depicted with two more decimals than captured in the database.
- categorical variables: percentages will be rounded to one decimal place and a percentage of 100% will be reported as 100%.
- the p-values will be rounded and displayed to 3 decimal places, values less than 0.001 will be displayed as 'p<0.001' and values higher than 0.999 will be displayed as 'p>0.999'.

This study has two parts Part A and Part B:

**Part A Analysis:** For Part A, summaries and analyses will be based on the data collected from the visits Week 0 to Week 12. Unless otherwise stated, the summary statistics and analyses will be presented for the following treatment groups:

- Sonelokimab 120 mg Q2W;
- Sonelokimab 60 mg Q2W;
- Sonelokimab 60 mg Q4W;
- Placebo;
- Adalimumab.
- Total sonelokimab (safety tables only)

**Part B:** For Part B no statistical testing will be performed. Summary statistics will be based on the data collected from the visits Week 12 to Week 24.

Unless otherwise stated, the summary statistics will be presented for the following treatment groups:

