### 8.9.2 Clinical Laboratory Evaluations

All central laboratory (hematology, biochemistry, urinalysis) parameters will be collected as described in [Appendix I](#).

Observed and change from baseline values for clinical laboratory parameters will be summarized using descriptive statistics by treatment group and visit separately for Part A and Part B. Shift from baseline to each scheduled assessment and the worst post treatment value according to normal ranges criteria will be presented. Shift from baseline to each scheduled assessment and the worst post treatment value according to CTCAEv5.0 criteria will also be presented. CTCAEv5.0 criteria are described in [Appendix L](#). Participants meeting any grade 3 criteria will also be listed.

In addition, the number and percentage of participants meeting the criteria for normal ranges in laboratory parameters will be summarized by treatment group separately for Part A and Part B.

Laboratory results together with the normal ranges will be listed, flagging values that are below or above the normal range. Serum/urine pregnancy tests assessments will be listed only.

Boxplots of the observed and change from baseline values for all clinical laboratory parameters will be presented by treatment group and visit for Part A and Part B. Reference lines for the normal ranges, that consistent across all participants being presented, will be displayed.

For participants with an AE of grade 3 or higher the hematology and chemistry lab parameters for that participant will be presented in a panel plot with a panel for each lab parameter. The x-axis will be the study week and the y-axis will be the absolute lab value.

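### Part B safety tables can count Week 12 values that belong to Part A, and adverse events around the switch that lack an onset time or a full date have no clear rule for which Part they enter

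*Combined protocol and SAP*

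**What the plan says.** - **Week 12 visit.** Protocol 8.3.3: "Assessments at Week 12 are both the final assessments for Part A and the first assessments for Part B". The first Part B dose is given at the same visit.
- **Part B data.** SAP 8.1, on Part B: "Summary statistics will be based on the data collected from the visits Week 12 to Week 24". SAP 7.1 defines baseline as the last measurement before the first Part A dose.
- **Value-based tables.** SAP 8.9.2 shows shifts to each visit and adds that "the worst post treatment value according to normal ranges criteria will be presented", with a CTCAE version alongside. SAP 8.9.3 and 8.9.5 count participants meeting vital-sign, weight and ECG criteria for Part A and Part B separately. None of these sections says which values are post-treatment for Part B.
- **Adverse events.** SAP 8.9.1: "TEAEs will be assigned to Part A, Part B and Part A+B using the event start date and time". Protocol 12.3.4 agrees: "AEs will be assigned to either Part A or Part B using the event start date and time". Part A takes events up to, but not beyond, Part B. Part B takes "Part B: events started on or after the first dose of study medication for Part B".
- **Day 1 rule.** SAP 8.9.1: "Adverse events with an onset on Day 1 which are based upon pre-dose lab tests will be considered as not treatment emergent". It applies to listed laboratory-type terms when the Day 1 sample time precedes the treatment start time. There is no counterpart for the first Part B dose.
- **Partial dates.** SAP 7.3.2 uses the 1st of the month when only the day is unknown and the onset month differs from that of the first dose. When day and month are missing and the year matches, the first dose date is used.

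**The concern.** Part B describes what happens after one treatment replaces another. An abnormality present at the Week 12 visit, before the new drug is given, belongs to the old one. If it enters the Part B column, the table credits the new drug with it. Events with an untimed or partial onset raise the same question, with no rule, or a one-sided rule, to settle it.

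The error passes into the pooled Part A+B event tables, because SAP 8.9.1 attributes those events through the Part to which they were assigned. It also reaches the exposure-adjusted rates. The SAP appendix on those rates ends observation for placebo and adalimumab participants at the first Part B dose, so a wrongly placed event sits over person-time that does not contain it.

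**Working it through.** The plan states no figure on this point, so there is none to reproduce.

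**1. Value-based tables.** Visits counted from the Schedule of Activities (Protocol Table 1). The last column adds the safety follow-up visit, because SAP 8.9 groups Part B with follow-up.

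| Assessment | Scheduled, Weeks 12 to 24 | Week 12 share | With follow-up |
|---|---|---|---|
| Chemistry, hematology | 12, 16, 20, 24 | 1 of 4 | 1 of 5 |
| Urinalysis | 12, 16, 24 | 1 of 3 | 1 of 4 |
| Vital signs | 12, 14, 16, 18, 20, 22, 24 | 1 of 7 | 1 of 8 |
| Weight | 12, 24 | 1 of 2 | 1 of 2 |
| ECG | 12 | 1 of 1 | 1 of 2 |

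That these values precede the dose is an assumption. Joint counts must be done before Part B allocation, and PK and antibody samples are pre-dose (Protocol 8.3.3, 11.6, 11.7), but no timing is stated for safety laboratory tests or ECG. One participant counted in the wrong column is 1/40 = 2.5 percentage points in a group of 40, or 1/10 = 10 points in a sequence of 10 (assumed size).

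**2. Events on the first Part B dose day.**

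- Onset time before the dose: Part A, under the date-and-time rule.
- Onset time after the dose: Part B.
- Date only: the Part A definition admits it, since that day is not beyond Part B. The Part B definition also admits it, since that day counts as on or after the dose. Protocol 12.3.4 requires onset after the first Part B treatment, which is a third wording.

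Date-only onsets are plausible, because Protocol 11.3.4 lists start and stop dates among the recorded variables and no clock time. The Day 1 rule works from the sample time, not the onset time, which suggests that the date-and-time rule alone was not thought sufficient on that day.

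**3. Partial dates.** Read the first dose date as the first dose of study treatment, and put the first Part B dose on Day 85, which is 84 days later. A Part B onset then never shares a calendar month with the first dose, so a missing day always becomes the 1st. The event lands in Part A only if its month is that of the first Part B dose and the dose was not on the 1st. Example: first dose 10 Jan 2023, first Part B dose 4 Apr 2023. An onset known only as April becomes 1 April (Part A); one known only as May becomes 1 May (Part B).

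Assumptions for the size: first doses spread evenly from 1 Oct 2022 to 15 Jul 2023 (288 dates), onsets uniform, end date missing or not before the first dose.

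- Day missing, onsets on Days 85 to 169: 288 × 85 = 24,480 combinations; 4,209 go to Part A, 4,209/24,480 = 17.2%.
- Day missing, Days 85 to 211: 288 × 127 = 36,576; 4,209/36,576 = 11.5%.
- Day and month missing: 97.0% (to Day 169) and 94.6% (to Day 211) go to Part A.
- First doses extended to 30 Sep 2023: 17.3% and 11.6% for a missing day; 88.2% and 82.5% for day and month.
- Part A events moved to Part B by the current rule when only the day is missing: 0%.

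**4. Where the drug changes.** From SAP Table 1: placebo to sonelokimab (all who enter Part B), adalimumab non-responders to sonelokimab, and sonelokimab 120 mg Q2W non-responders to adalimumab. Every other sequence keeps its drug, though non-responders on 60 mg change dose.

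**The case against.** The best reply is that the assignment rule uses date and time in both documents. A reader might infer that the plan credits pre-dose Week 12 findings to the Part B drug as a matter of course. It does not: a timed pre-dose event belongs to Part A, and only the untimed case is open. The Day 1 analogy is also imperfect. That rule separates emergent from non-emergent events, whereas a Week 12 event is emergent either way. Its named lipid terms have little Week 12 counterpart, because the fasting panel is scheduled at Day 1 and end of treatment.

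A reader might also infer that Part B events with a missing day are generally moved to Part A. That holds only in the calendar month of the first Part B dose; 83 to 88% stay in Part B under the assumptions above. SAP 7.3.2 uses the imputed date to classify events as pre-treatment, emergent or post-treatment and is silent on Part, so a Part-specific reading of first dose date is possible.

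Further, by-visit tables label Week 12, all data are listed, safety is descriptive, and the SAP keeps US participants out of Part B. These points limit the consequence. They do not answer the worst-value and any-abnormality counts, which lose the visit label and do not depend on event times.

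**Conclusion.** The concern holds in limited form. The value-based limb is the firmest: applied as written, the plan lets Week 12 values into Part B counts, and for ECG no other recording is scheduled until safety follow-up. It rests on the assumption that Week 12 values precede the dose. The switch-day limb is an ambiguity confined to onsets without a time. The partial-date limb is a one-sided default: small to moderate for a missing day, large when the month is also missing. Its size depends on the assumed enrollment dates and uniform onsets.

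The switch-day limb can push events toward either drug, while the partial-date default pushes them back to the earlier one, so no net direction can be claimed. The documents give no count of affected events. The primary and key secondary efficacy analyses are untouched. The changes are worth making because they alter reported safety counts by treatment at little cost.

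**What to change.** 1. **SAP 8.1 and 8.9.2 to 8.9.5.** Base Part B worst-value, shift and abnormality-criteria tables only on values after the first Part B dose, and show Week 12 as the Part B starting value. Select by date and time, not by visit label, because the Week 12 laboratory window in SAP 7.2 runs from Day 72 to Day 99 and straddles the dose. The Part B ECG table will then hold no scheduled on-treatment recording, which the report should state.
2. **SAP 8.9.1.** Extend the Day 1 pre-dose laboratory rule to the first Part B dose day, sending such events to Part A. Make the Part A and Part B definitions mutually exclusive and consistent with Protocol 12.3.4, and state a rule for a missing onset time. Correct the pointer to Section 8.3.2; the date rules are in 7.3.2.
3. **SAP 7.3.2.** Add a Part B anchor for partial dates, and report a sensitivity count with ambiguous events assigned each way.

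The cost is SAP wording and a few lines of programming. The third change has a real downside. Imputing to the Part B dose date would bring the day-missing leak from Part B to 0%, but under the same assumptions it would move 4,241 of 24,192 (288 × 84) day-missing Part A onsets, 17.5%, into Part B. For dates with only a year, about 85% of Part A onsets share the calendar year of the first Part B dose (88% with the later enrollment end) and would move. Neither default is unbiased, so the two-way count matters more than the choice of anchor.
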